## 2. Study design

The proposed study is an open-label, randomized, intervention study in patients tested positive for SARS-CoV2 on the ward. Forty patients will be enrolled in a 1:1 randomized fashion for intervention (Ivanadelumab administration) versus controls (standard treatment). To be able to randomize forty patients within the study duration, a multi-center approach is chosen.

We have chosen to perform this trial in patients that are Sars-COV2 positive as we believe they can directly benefit from this intervention. As such it merits preference over testing this drug first in healthy volunteers to demonstrate the safety of intravenous administration and then move into patients with COVID19 disease. We argue this is best done in a combined fashion.

### 3. Subject population

#### 3.1 Number of subjects and subject selection

Fourty patients will be randomized 1:1 for the intervention with lanadelumab iv. Twenty SARS-COV2 positive patients treated with lanadelumab 300 mg IV on day 1, followed by a second dose of lanadelumab 300 mg IV on day 4. The other 20 lanadelumab patients will receive the same treatment algorithm while NOT receiving lanadelumab. The estimated number of patients being treated for COVID disease is difficult to predict. Currently about 20% of the COVID-19 patients are hospitalized and out of these patients about 20% is admitted to the ICU.

These will be patients from the following centers:

- Amsterdam UMC, Amsterdam
- Radboud University Medical center, Nijmegen,
- University Medical Center Utrecht, Utrecht,
- Rijnstate Hospital, Arnhem
- Flevoziekenhuis, Almere

#### 3.2 Inclusion criteria

Subjects must meet all of the following inclusion criteria to be eligible for participation in this study:

1. Patient is SARS-COV2 positive
2. Without oxygen a saturation below 90% or / and At least 3L/min oxygen dependent
3. Patient is 16 years and older

#### 3.3 Exclusion criteria

Subjects who meet any of the following criteria will be excluded from participation in this study:

1. Has previously participated in this study
2. Acute myocardial or cerebral ischemic event at time of enrolment
3. Receiving an agent that is specified as an intervention in this domain as a usual medication prior to this hospitalization will exclude a patient from receiving that agent
4. A baseline alanine aminotransferase or an aspartate aminotransferase that is more than five times the upper limit of normal
5. Patient is known hypersensitive to full human monoclonal antibodies.
6. Patient is pregnant or breast feeding

#### 3.4 Study duration

The expected duration of the study for an individual patient will be as long as the patient is hospitalized. The estimated length of time needed to complete the entire study will be one month.

#### 3.5 Removal of subjects from the study

The investigator may terminate participation if:

- There is violation of protocol
- It is in the best interest of the subject
- Patients that are transferred to the ICU will be followed up for safety and if possible samples will be taken, but are considered to have reached a study endpoint.

Subjects dropping out before the final dose has been given, will not be replaced. Patients are regarded evaluable after both treatment days are completed.

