| ANALYTICAL AND STATISTICAL METHODS                                                                            |                                                                                                                                                                                                                                                                                                                                                                                                                                                                                                                                                                                                                                                                                                                                                                                                                                                                                                                                                                                                                 |
| Safety, demographics and statistics                                                                    | 
In general, all subjects who completed the study will be included in the statistical evaluation for demographics and safety. Subjects can be excluded from the statistical analysis if no reliable parameters can be determined. Moreover, subjects can be excluded from data evaluation if justified by circumstances (e.g. no correct drug administration). Patients are regarded evaluable after administration of the first lanadelumab dose.
 
Statistical analysis will be carried out using SPSS software version 20 [SPSS Inc.]. Descriptive statistics will be calculated using Excel software [Microsoft Corporation].
                                                                                                                                                                                                                                                                                                                                                                    |

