### **3.6 Replacement of subjects**

Subjects will be replaced if an incorrect lanadelumab dose was given, other dropouts will not be replaced in case of dropouts as the study has an explorative nature.

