## 4. Treatment

In the current study subjects will be treated with lanadelumab 300 mg IV on day 1 followed by a second dose of lanadelumab 300mg IV on day 4.

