### 5.3 Method of assigning subjects to treatment groups

Subject will be randomized in a 1:1 ratio to receive lanadelumab or standard clinical management without drug intervention. Each group will contain 20 participants.

Randomization will be done by Castor. Each patient will be entered into the Castor system and randomization will be allocated immediately. This is a standard procedure as deployed in other trials.

Each site has drug on site for at least one patient and therefor randomisation to the intervention arm can be acted upon immediately. Considering the small sample size there will be no stratification.

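### The protocol gives two conflicting evaluability rules, neither workable for controls, and ties its analysis sets to events after randomisation

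*Protocol*

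**What the plan says.** Two statements define evaluability.

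- Protocol Synopsis, safety, demographics and statistics row: "Patients are regarded evaluable after administration of the first lanadelumab dose".
- Protocol section 3.5: "Patients are regarded evaluable after both treatment days are completed". The sentence just before it reads "Subjects dropping out before the final dose has been given, will not be replaced".

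Section 4 gives the schedule as "lanadelumab 300 mg IV on day 1 followed by a second dose of lanadelumab 300mg IV on day 4". Section 5.3 describes the comparison: "Subject will be randomized in a 1:1 ratio to receive lanadelumab or standard clinical management without drug intervention".

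Three further rules bear on who is analysed.

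- The Synopsis says that, in general, "all subjects who completed the study will be included in the statistical evaluation for demographics and safety".
- The Synopsis also says "subjects can be excluded from data evaluation if justified by circumstances (e.g. no correct drug administration", as an example.
- Section 3.6 says "Subjects will be replaced if an incorrect lanadelumab dose was given"; other dropouts are not replaced.

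Two provisions point towards counting failures. Section 3.5 treats ICU transfer as reaching a study endpoint, with continued safety follow-up. Section 7.3 imputes the highest recorded oxygen value after death, as a sensitivity analysis. Nothing in the protocol says that all randomised patients are analysed in their assigned arm.

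**The concern.** Whether a patient receives a second dose on day 4 depends on what happens after randomisation: death, ICU transfer, recovery or toxicity. A rule that makes analysis depend on it selects patients by their course. If the rule bites in one arm more than in the other, the arms are no longer comparable and a difference can appear without any drug effect.

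Safety is affected most directly. Showing that intravenous lanadelumab is safe is one of the two primary objectives (section 1.3), and section 1.2 says this route was not tested in the HAE clinical package. Under section 3.7 a severe attributable event leads to an evaluation of whether the second dose can be given. If it is withheld, section 3.5 can make that patient non-evaluable, and if the patient also leaves the study, the Synopsis sentence on completers does not cover them. The patient who says most about harm is one these rules could remove.

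This is not a detail left to a statistical analysis plan. The protocol itself states the conflicting rules, and any such plan would have to depart from one of them.

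**Working it through.** The protocol states no figure on this point that could be reproduced: no power, effect size or significance level. So the rules are compared first, and the possible size is then illustrated.

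**Step 1. The two rules by type of patient**

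| Patient | Synopsis rule | Section 3.5 rule |
|---|---|---|
| Lanadelumab arm, both doses | evaluable | evaluable |
| Lanadelumab arm, one dose only | evaluable | not evaluable, if treatment days means dosing days |
| Lanadelumab arm, no dose | not evaluable | not evaluable |
| Randomised control | never evaluable, read literally | undefined, unless it means reaching day 4 |

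The second row is a direct contradiction. It is a live case: footnote e to Table 1 (section 6.1) sets PK sampling for patients who get only one dose. The fourth row shows that neither rule gives a usable definition for half of the trial.

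**Step 2. Conflict inside section 3.5**

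A treated patient transferred to ICU before the second dose has reached a study endpoint by one sentence and is non-evaluable by another. Section 7.3 does not settle this: its imputation covers death only, and only as a sensitivity analysis.

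**Step 3. Illustration on ICU admission**

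Inputs:
- 20 patients per arm (section 5.3).
- p = 0.20, the ICU share of hospitalised patients in section 3.1, taken for both arms, so no drug effect.
- f = share of ICU transfers before the second dose. The protocol does not give it; 0.25 to 0.75 is assumed.
- The section 3.5 rule applied to the lanadelumab arm only, which is also an assumption.

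Apparent treated rate = p(1 − f) / (1 − pf). Expected number lost = 20pf. Chance of losing at least one = 1 − (1 − pf)^20.

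| f | Treated rate among evaluable | Controls | Ratio | Expected lost | Chance of at least one lost |
|---|---|---|---|---|---|
| 0.25 | 0.15/0.95 = 15.8% | 20% | 0.79 | 1 | 64% |
| 0.50 | 0.10/0.90 = 11.1% | 20% | 0.56 | 2 | 88% |
| 0.75 | 0.05/0.85 = 5.9% | 20% | 0.29 | 3 | 96% |

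**Step 4. The opposite bias**

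If a share r of treated patients also becomes non-evaluable through early recovery, the apparent rate is p(1 − f) / (1 − pf − r). It returns to p when r = f(1 − p), which is 0.20, 0.40 and 0.60 for the three values of f, or 4, 8 and 12 of 20 patients. A larger r makes lanadelumab look worse. The protocol gives no value for r, but early recovery is not remote: section 1.2 reports 4 of 9 ward patients off oxygen within 10 to 35 hours of icatibant.

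**Step 5. Illustration on a continuous oxygen outcome**

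The primary endpoint is repeated oxygen use (section 7.3). It was approximated by one normal value per patient in a simulation with 20 per arm, 20% failures assumed 1 to 3 SD worse, no drug effect, a two-sided 5% t-test and 8,000 runs per setting. Early failures were removed from the treated arm only, and early recoveries were not modelled. The spurious benefit was 0.05 to 0.13 SD at f = 0.25 and 0.09 to 0.26 SD at f = 0.50. The chance of a false significant result favouring lanadelumab was 3.6% to 4.4% and 4.1% to 7.3%, against a nominal 2.5%.

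**Step 6. After the fix**

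With all randomised patients analysed as assigned, nobody is lost through these rules and the expected difference under no effect is 20% − 20% = 0.

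**The case against.** A reader might infer that early failures are certain to leave the lanadelumab arm while matching controls stay. The protocol does not say this. The section 3.5 sentence does not name lanadelumab, and controls follow the same treatment algorithm without the drug (section 3.1). The day 4 biomarker sampling is not marked as intervention-only (Table 1), so a day 4 rule for both arms is a possible reading. The dose reading comes from the neighbouring sentence and the schedule. The objection stands against any claim of certain one-arm deletion. It does not rescue the rule: applied to both arms, it would still select on the first days after randomisation and still contradict the Synopsis.

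A reader might also infer that the main analysis, oxygen use included, keeps completers only. The Synopsis sentence says in general, covers demographics and safety, and does not say only. It applies to both arms, and since section 3.4 ties an individual's duration to the hospital stay, a one-dose patient may still complete. What remains is that safety, a primary objective, is described through completers.

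The ICU-endpoint and death-imputation provisions show an intent to count failures. That stands, but they conflict with the evaluability sentence and do not override it.

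Replacement under section 3.6 adds a patient; it does not say that the replaced patient's data are discarded. Exclusion for incorrect administration is permitted, not required. Both leave the handling open.

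Finally, the study is hypothesis-generating and largely descriptive. That explains the absence of a sample size calculation. It does not justify contradictory analysis sets in a randomised comparison.

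**Conclusion.** The point holds as a contradiction with a possible bias, not as a demonstrated one. Certain from the text: the Synopsis and section 3.5 disagree on one-dose patients, neither defines evaluability usably for controls, section 3.5 conflicts with itself over early ICU transfer, and replacement is tied to lanadelumab dosing, so it can arise in one arm only. Conditional: the amount of bias.

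The figures of 15.8% to 5.9% against 20% require the two-day rule to be applied to the lanadelumab arm only, the general 20% ICU rate to hold for this population, and an assumed 25% to 75% of transfers to precede the second dose. They concern an outcome that is not the primary one and amount to 1 to 3 patients out of 20. The ratio of 0.29 is the far end of a one-sided calculation and should not be read as the expected error. Early recoveries push the other way, so the net direction is uncertain.

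The wording should be corrected before analysis, because following it can bias the comparison and drop early-harmed patients from the safety evaluation.

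**What to change.** Reconcile the Synopsis, section 3.5 and section 3.6 so that they state one set of definitions:

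- **Efficacy:** all 40 randomised patients, and any replacements, in the arm assigned, whatever doses were received.
- **Safety:** every patient given any amount of lanadelumab, and all randomised controls. Delete the restriction to those who completed the study.
- **Incorrect dosing and replacement:** keep any replaced or incorrectly dosed patient in both sets, and remove incorrect administration as a ground for exclusion from them.
- **Two-dose set:** use it only as a supportive PK or per-protocol set, labelled as such.
- **ICU transfer before the second dose:** state that it counts as the endpoint section 3.5 says it is.

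These changes concern analysis sets only and alter no dosing or clinical rule. The cost is a wording amendment to three places. The downside is that the estimate includes patients with incomplete dosing, so it describes the effect of assignment to lanadelumab and not that of receiving both doses; the supportive set can address the latter.

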### **3.6 Replacement of subjects**

Subjects will be replaced if an incorrect lanadelumab dose was given, other dropouts will not be replaced in case of dropouts as the study has an explorative nature.

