### 4.3 Safety and potential risks

For general safety information we refer to the SmPC of lanadelumab.

Briefly stated it has the following information:

Hypersensitivity is an important identified risk and is discussed in the warnings and precautions of the reference labelling. In case of a severe hypersensitivity reaction, administration of TAKHZYRO must be stopped immediately and appropriate treatment must be initiated.

Immunogenicity is an important potential risk for lanadelumab and is monitored closely. The known potential risks of disordered coagulation associated with monoclonal antibodies have been characterized and no unexpected signals were identified.

The most commonly occurring adverse events with greater frequency in the lanadelumab treatment groups were injection site reactions (34.1% placebo, 52.4% lanadelumab) and dizziness (0% placebo, 6.0% lanadelumab). Less common reactions in the lanadelumab group compared to placebo include hypersensitivity (1% vs. 0%), increased liver enzymes (2% compared to 0%). An open-label extension study to evaluate the long-term safety and efficacy of lanadelumab for prevention of HAE attacks is ongoing. (Riedl et al., 2017). Pharmacokinetic analyses showed that the use of concomitant medications such as analgesic, antibacterial, antihistamine, anti-inflammatory, and antirheumatic medications used in the treatment of HAE had no effect on the pharmacokinetic properties of lanadelumab, suggesting that the drug-drug interaction potential of those evaluated drug classes is low. Similar observations were made for rescue medications, including plasma-derived and recombinant C1-INH, ecallantide, and icatibant, used for acute treatment of HAE attacks.

In this study two dosages of 300 mg intravenous lanadelumab are given on day 1 and day 4. The cumulative dose of 600 mg per week is higher than the current licensed dose for prevention of HAE. Even with a second dose given on day 4 of treatment the predicted drug concentrations remain far below the maximal tolerable dose. [see pop-PKPD modeling file with simulations]. We do not expect additional toxicity of the approach chosen.

Additional safety information to support for lanadelumab given as intravenous administration

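### The replacement rule in section 3.6 can in practice be triggered only in the lanadelumab arm, leaves an incorrect dose and the allocation of replacements undefined, and with the synopsis exclusions lets dosed patients leave the comparison and the safety rate

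*Protocol*

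**What the plan says.** Section 3.6 of the protocol sets one ground for replacement: "Subjects will be replaced if an incorrect lanadelumab dose was given, other dropouts will not be replaced in case of dropouts". It gives the exploratory nature of the study as the reason for not replacing the others. Section 3.5 states, without exception, "Subjects dropping out before the final dose has been given, will not be replaced".

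On allocation, section 5.3 says "Subject will be randomized in a 1:1 ratio to receive lanadelumab or standard clinical management without drug intervention", with 20 participants in each group, no stratification, and "Each patient will be entered into the Castor system and randomization will be allocated immediately". It does not mention replacements.

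On who is analysed, section 3.5 says "Patients are regarded evaluable after both treatment days are completed", while the synopsis (Safety, demographics and statistics) says "Patients are regarded evaluable after administration of the first lanadelumab dose". The same synopsis row says that, in general, those who completed the study enter the demographic and safety evaluation, and adds that "subjects can be excluded from data evaluation if justified by circumstances (e.g. no correct drug administration").

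On interrupted infusions, section 4.3 says "In case of a severe hypersensitivity reaction, administration of TAKHZYRO must be stopped immediately".

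**The concern.** The trigger is a post-randomisation event tied to one treatment. Barring a control dosed by mistake, no control can be replaced. Whoever judges a dose incorrect knows the arm and may already know how the patient responded. The protocol gives no definition to constrain that judgement.

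Two things are at stake. The first is the oxygen comparison: one arm can lose randomised patients and gain later ones, while the other stays as randomised. The second is the primary objective on the safety of intravenous administration. Patients with dosing errors, and possibly those with incomplete infusions, bear directly on that objective, and the synopsis permits leaving them out.

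**Working it through.** **Plan's own figure.** 40 patients at 1:1 gives 40 × 1/2 = 20 per arm, as section 5.3 states. Section 7.1 says that no formal sample size calculation was done, so no power target depends on replacement.

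**Sections 3.5 and 3.6 side by side.**

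| Patient | Section 3.5 | Section 3.6 |
|---|---|---|
| Correctly dosed, leaves before the final dose | not replaced | not replaced |
| Incorrectly dosed, stays to the end | silent | replaced |
| Incorrectly dosed, leaves before the final dose | not replaced | replaced |

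The sections collide only in the last row. That row is plausible: section 3.5 lets the investigator end participation for a protocol violation, and a wrong first dose could be treated as one.

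**How a replacement enters.** Let k lanadelumab patients be replaced out of 20.

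- *Assigned directly to lanadelumab.* The share of the final 20 who did not come through the 1:1 allocation is k/20, which is 5% for k = 1 and 10% for k = 2. The share of dosed patients displaced is k/(20 + k): 1/21 = 4.8% and 2/22 = 9.1%.
- *Allocated 1:1 through Castor (simple randomisation assumed).* The chance that all k land on lanadelumab is 0.5^k: 50% for k = 1 and 25% for k = 2. The expected number of correctly dosed lanadelumab patients is 20 − k + k/2, against 20 + k/2 controls. For k = 2 this is 19 against 21.
- *Continuing 1:1 until lanadelumab is back at 20.* This takes about 2k extra patients and gives 20 against 20 + k. For k = 2 that is four extra patients and arms of 20 and 22.

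So the rule either does not reliably replace anyone or steps outside the allocation.

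**Could an infusion stopped early be classed as incorrect?** In the section 4.1 ramp, at most 30 mg of 300 mg (10%) has been given by 20 minutes and at most 100 mg (33%) by 40 minutes. A stopped infusion therefore delivers an incomplete dose. The protocol does not say whether incomplete counts as incorrect.

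**How often this might arise.** The chance of at least one stopped infusion in 20 patients is 1 − (1 − p)^20. Section 4.3 reports hypersensitivity of any severity in 1% on lanadelumab in the earlier hereditary angioedema data. Using p = 1% as a stand-in gives 18%. Assumed rates of 2%, 5% and 10% give 33%, 64% and 88%.

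**Effect on a safety rate.** Clopper-Pearson 95% limits, if one patient with an event leaves the denominator and is replaced:

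- All dosed patients kept: 1/21 = 4.8%. The lower limit is 1 − 0.975^(1/21) = 0.1%. The upper limit is the 97.5th percentile of Beta(2, 20), 23.8%.
- Patient swapped out: 0/20 = 0%. The upper limit is 1 − 0.025^(1/20) = 16.8%.

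Section 3.6 does not itself remove the original patient from the denominator. The synopsis text permits it.

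**The case against.** Much can be said for the protocol.

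- **Allocation.** Section 5.3 puts each patient through Castor and exempts nobody. A reader might infer that replacements have no randomised route, or that the lanadelumab arm is necessarily refilled. The text supports neither inference, because a replacement sent through Castor may become a control. What stands is that the route is unstated, and that fresh 1:1 allocation does not achieve replacement.
- **Conflict with section 3.5.** By speaking of other dropouts, section 3.6 can be read as carving out an exception. That narrows the clash to one kind of patient, but section 3.5 does not acknowledge the exception.
- **Stopped infusions.** An incorrect dose most naturally means a dosing error, and stopping an infusion as section 4.3 requires is compliance with the protocol. A reader might infer that a reaction could be hidden by swapping the patient out. The documents do not support that. Section 3.7 stops the study for evaluation after one attributable severe event. Section 6.3 requires recording and reporting of adverse events. Section 9.1.8 requires case report forms and outcome documentation for patients who do not finish. Section 5.5 has every administration supervised and recorded. The event would be on file, so what remains exposed is the reported rate and the arm comparison.
- **Denominator.** Replacement adds a patient and need not delete one, and the two intervals overlap heavily. This is fair, so the figures are an illustration. The synopsis nevertheless permits the deletion.
- **Scale and status.** The trial is small and hypothesis-generating, and analysis sets may be detailed in a statistical analysis plan that is not at hand. But replacement and allocation are conduct rules fixed in this protocol, and the exclusion permission is stated in its synopsis.

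**Conclusion.** The point holds in a limited form. Section 3.6 contains a post-randomisation replacement rule that in practice only the lanadelumab arm can trigger. Its trigger is undefined, its allocation route is unstated, and it is unreconciled with section 3.5 for incorrectly dosed patients who leave before the final dose. Combined with the synopsis, it allows a patient with a dosing error, or on one reading an infusion stopped early, to be replaced and left out of both the oxygen comparison and the safety rate.

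Each such patient is 5% of the arm. The shift from 1/21 to 0/20 assumes that one patient with an event is removed from the denominator, which the synopsis permits and section 3.6 does not state. The size and direction of any bias in the oxygen comparison cannot be derived from the protocol, since dosing errors need not be related to prognosis. This should be corrected, but it is not evidence that events would go unreported.

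**What to change.** 1. In section 3.6, delete the replacement sentence so that sections 3.5 and 3.6 agree that no randomised patient is replaced. Alternatively, state that any additional patient is allocated 1:1 through Castor to either arm and does not displace the original.
2. Amend the synopsis text on exclusions and completers. Every randomised patient stays in the allocated arm for the oxygen comparison. Every patient who received any lanadelumab is in the safety data, with the amount actually infused. Changing section 3.6 alone would leave the exclusion permission in place.
3. Leaving out incorrectly dosed patients may remain as a sensitivity or pharmacokinetic analysis.

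The cost is one sentence in section 3.6 and a short edit to the synopsis, with no sample size calculation to redo. The downside is slight dilution of the effect estimate if one or two incorrectly dosed patients remain in the lanadelumab arm. If top-ups are allowed, the arms may end slightly unequal. No dose or clinical rule changes.
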